	Time-to-imaging decision	Compare time from triage to CT decision between arms.	Evaluate whether biomarker access accelerates or delays decision-making.
	Disposition flow	Evaluate differences in ED-to-disposition pathways with vs. without biomarker data.	ED throughput times, floor/ICU admissions.
Secondary (validation) full cohort as single arm	Diagnostic accuracy	Determine sensitivity, specificity, NPV, and PPV of biomarkers vs. CT findings for intracranial lesions.	Biomarker levels vs. CT results.
	Kinetic profiling	Evaluate the kinetics and temporal profile of GFAP/UCH-L1 across 0, 8, 16, and 24 h.	Serial biomarker levels, time-to-peak and decay curves.
	Predictive modeling	Build multivariable models using biomarkers and clinical data to predict imaging-positive patients.	ROC curves, AUC, logistic regression outputs.
	Triage integration	Assess biomarker utility in supplementing current BIG criteria for TBI triage.	Sensitivity/specificity when combined with BIG criteria.
	Outcome prediction	Evaluate whether biomarker levels predict functional outcomes or neurologic decline.	Correlation with GOSE score, readmission, or symptom progression.
Secondary (implementation) only published cohort	Implementation feasibility	Assess provider adherence to biomarker interpretation guidelines in the biomarker-published arm.	Understand clinical adoption barriers and fidelity to protocol including provider and patient variables
	Patient perception	Evaluate patient understanding and satisfaction with biomarker-driven decision-making.	Gain insights into trust and acceptance of non-imaging diagnostics.

TBI, traumatic brain injury; CT, computed tomography; ED, emergency department; LOS, length of stay; ICEA, incremental cost-effectiveness analysis; GCS, Glasgow Coma Scale; GOS, Glasgow Outcome Scale; GOSE, Glasgow Outcome Scale-Extended; ICU, intensive care unit; NPV, Negative predictive value; PPV, Positive predictive value; ROC, Receiver Operating Characteristic; AUC, Area under the curve; BIG, Brain Injury Guidelines.

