### Study design and methods

The BRAIN-CT trial is a single-center prospective, randomized, open-label, blinded endpoint study conducted in the ED of Grady Memorial Hospital, a level I trauma center. After completion of initial screening, 350 adults aged 18–85 years will be randomized 1:1 to either a biomarker-published arm (real-time GFAP and UCH-L1 values released to clinicians coupled to education on biomarker data) or a biomarker-blinded arm (standard care without biomarker disclosure). The study flow chart is provided in Figure 1. Allocation uses computer-generated permuted blocks stratified by age (3 Strata: 18–30, 31–50, 51–85 years), biological sex, race (2 Strata: Black, Not Black), Glascow Coma Scale (GCS) (2 Strata: 15, 13–14) and baseline Canadian CT Head Rule risk category (3 Strata: High Risk, Medium Risk, None) to balance key factors in routine decision making. The maximum sample size remains 350 participants for the initially planned cohort. Outcome adjudicators are masked to treatment assignments. Given the pre-existing FDA-approval of the use of the TBI biomarker testing in mild-TBI, the study is deemed no more than minimal risk to participants and a data safety and monitoring board was not required. This study is registered with clinicaltrials.gov (Identifier: NCT06932588), and the study was approved by the Institutional Review Board at Emory University and the Research Oversight Committee at Grady Memorial Hospital.

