### Procedures for the published biomarker arm

For the published arm, providers are requested to pause imaging orders until biomarker data is available which requires around 15 min delay. When biomarker data is available, these are printed and provided timely to the provider along with the cut-off for an elevated test. The cut-off used are 65 pg./mL for GFAP and 360 pg./mL for UCH-L1. The provider will also be handed a refresher education on the published data on the negative predictive value (NPV) and positive predictive value (PPV) of the test. The decision whether to pursue a CT of the head will be left to the provider and patient discussion considering the biomarker data. A test is considered non-elevated only if both biomarkers were below the pre-defined cut-off.

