### Secondary analyses

Relevant secondary analyses reported in Table 2 will be studies as described below:

Assess the impact of biomarker result access on physician decision-making for CT use (Time to obtaining CT head, *t*-test).Hospital Length of stay in published versus blinded group (*t*-test).Hospital costs for published versus blinded group (Incremental cost effectiveness analysis).GCS and GOS-E comparison in published versus blinded groups at 6 and 12 months (Ordinal logistic regressions).Compare rates of discharge, floor admission, and ICU admission between the published and blinded groups (logistic regression for each outcome, taking admission GCS and age as covariates).Within all patients, define the sensitivity and specificity for predicting GOS-E scores at 6 and 12 months for biomarker test as well as when combined with clinical variables and BIG criteria (ROC analysis).Within the published group, study predictors of adherence to biomarker-based guidelines among providers (logistic regression).

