### Sample size justification

Based on preliminary data from published studies, we defined a clinically significant impact to be attained at 15% reduction in the rate of CT head imaging in the published group, assuming 70% baseline CT utilization (23). Adjusting for an alpha of 5%, a total of 300 evaluable patients will be required (150/arm) to achieve at least 80% power to reject the null hypothesis. To account for patient withdrawal (change in exam before blood draw, leaving against medical advice, etc.), we will plan to target a maximum of 350 subjects enrolled.

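### The provider-adherence model is named as logistic regression with no allowance for repeated decisions by the same provider, so intervals for provider-level predictors may be too narrow

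*Protocol article*

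**What the plan says.** The last item under Secondary analyses in the protocol article is restricted to the published group and will "study predictors of adherence to biomarker-based guidelines among providers (logistic regression"). No random effect, cluster term or robust variance is named. Table 2 (Study objective) gives the matching implementation objective as "Assess provider adherence to biomarker interpretation guidelines in the biomarker-published arm", and its outcome column reads "Understand clinical adoption barriers and fidelity to protocol including provider and patient variables". The model is therefore meant to carry predictors at two levels, provider and patient.

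Adherence is observed once per patient, but a provider takes part in every decision. Under Procedures for the published biomarker arm: "The decision whether to pursue a CT of the head will be left to the provider and patient discussion considering the biomarker data".

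Study design and methods describes a "single-center prospective, randomized, open-label, blinded endpoint study" in which "350 adults aged 18–85 years will be randomized 1:1". That puts about 175 patients in the published arm. Sample size justification plans for 150 evaluable patients per arm.

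The article does not say how many providers take part, how many published-arm patients each one sees, or how adherence is scored.

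**The concern.** A provider characteristic such as role or experience takes the same value for every patient that provider sees. If one provider's decisions resemble each other, ten patients seen by one provider carry less information about that characteristic than ten patients seen by ten providers. Logistic regression in its usual form counts them equally, so its standard errors for provider-level predictors are too small and its tests reject too often.

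The article itself gives reason to expect such resemblance. Rationale for randomization lists clinicians' habits of deciding among the confounders and calls CT decisions subjective. Expected impact of the proposed trial names clinicians' own preferences and fear of litigation as reasons why earlier decision rules were taken up unevenly.

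What is at stake is the implementation aim. The model is meant to show what hinders adoption. Intervals that are too narrow could direct later implementation work at provider characteristics that have no bearing on adherence.

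**Working it through.** The plan gives no sample size, power or precision for this analysis, so there is no figure of its own to reproduce. The statement that "a total of 300 evaluable patients will be required (150/arm) to achieve at least 80% power to reject the null hypothesis" concerns the CT-rate comparison and is used here only for the size of the published arm.

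**Inputs from the article**
- Published arm: 350/2 = 175 randomized, 150 evaluable.
- Method: logistic regression. Predictors: provider and patient variables.
- One emergency department.

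**Inputs assumed, because the article does not give them**
- Number of providers K: 15 to 80.
- Intraclass correlation (ICC) on the latent (logit) scale: 0 to 0.20.
- Adherence: 60% or 70%.

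**Step 1, closed form.** With m = n/K patients per provider, the design effect for a provider-level predictor is DE = 1 + (m − 1) × ICC. The naive standard error is too small by the factor √DE, and a nominal 5% two-sided test has actual size 2 × [1 − Φ(1.96/√DE)].

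The ICC in this formula belongs on the binary scale. At 60% adherence a latent ICC of 0.20 is about 0.147 on that scale. For n = 175 and K = 15:
- m = 175/15 = 11.67
- DE = 1 + 10.67 × 0.147 = 2.57, and √DE = 1.60
- size = 2 × [1 − Φ(1.96/1.60)] ≈ 22%

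Putting the latent 0.20 in directly would give DE = 1 + 10.67 × 0.20 = 3.13, which overstates the effect.

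**Step 2, simulation, 175 patients.** A null binary predictor and a provider random intercept were simulated, and a naive logistic model was fitted. Type I error for a provider-level predictor, adherence 70%, 1,500 replicates per cell:

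| Providers | ICC 0 | ICC 0.05 | ICC 0.10 | ICC 0.20 |
|---|---|---|---|---|
| 20 | 4.7% | 8.3% | 10.7% | 17.7% |
| 40 | 5.3% | 6.7% | 9.1% | 12.7% |
| 80 | 4.5% | 5.7% | 6.3% | 8.7% |

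The Monte Carlo standard error near 5% is √(0.05 × 0.95/1500) = 0.6 percentage points. A separate simulation over latent ICC 0.05 to 0.20 gave about 11–24% with 15 providers, 7–15% with 30 and 6–9% with 60. The upper end agrees with the closed-form 22%.

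**Step 3, patient-level predictors.** In the same 1,500-replicate runs the type I error for a patient-level predictor stayed between 3.9% and 5.9% in every cell. The problem is confined to provider variables.

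**Step 4, a smaller analysis set.** Adherence might be scored only when the result is non-elevated. The Introduction puts specificity below 40%, so at most about 0.40 × 175 = 70 patients would qualify. With 15 providers, m = 70/15 = 4.67 and DE = 1 + 3.67 × 0.147 = 1.54, so the size is about 11.4% at latent ICC 0.20 and 6.7% at 0.05. With 30 providers it is 5.6–7.3%, and with 60 it is 5.1–5.3%. Simulation gives about 5–13% over the whole range.

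**Step 5, the limit.** With one patient per provider (m = 1) or ICC = 0, DE = 1 and the size is 5%.

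**The case against.** The strongest objection is that a journal article condenses the protocol. Each secondary analysis gets a short method label in brackets, and variance estimation is commonly left to a statistical analysis plan, which is not shown here. A mixed-effects or GEE logistic model is still logistic regression, and nothing in the article excludes one. This limits how certain the point can be. It does not dispose of it, because the article names a method, and in its usual meaning that method assumes independent observations. The same list is more specific elsewhere: it names ordinal models for the GCS and GOS-E comparison, and covariates for the disposition outcomes.

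Second, a reader might infer that each provider is known to treat several published-arm patients. The article does not say so. The inference is reasonable, since avoiding any repetition would take 150 to 175 different providers in one department with one published-arm patient each, but it remains an inference.

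Third, a reader might conclude that false predictors will be reported. The figures do not support that. Inflation is small with many providers or with a restricted analysis set, and becomes large only when few providers and a high correlation occur together. Neither is documented. Patient variables, which Table 2 also names, are hardly affected.

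Finally, the analysis is one of two implementation objectives, with no alpha or success rule attached. That bears on the weight of the point and leaves the mechanism intact.

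**Conclusion.** The point holds in a limited form. Followed as written, the adherence model has no stated allowance for repeated decisions by the same provider, while some of its predictors are fixed within provider. If providers contribute more than one patient and their decisions are correlated, standard errors for those predictors are too small.

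The size cannot be fixed from the article. For 175 patients, 15 to 60 providers and latent ICC 0.05 to 0.20, a nominal 5% test has an actual type I error of about 6% to 24%. With some 70 non-elevated results it is about 5% to 13%. It is 5% if no provider repeats or the ICC is zero. Confidence is moderate, because the provider count, the patients per provider and the ICC are all assumed.

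The consequence is confined to provider-level findings in a secondary implementation analysis. The randomized comparison of CT rates is not touched.

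**What to change.** Record a provider identifier for each published-arm CT decision. In Secondary analyses, replace the bare method label with one of two models: logistic regression with a provider random intercept, or GEE clustered by provider with small-sample-corrected robust errors. In simulation, cluster-robust errors referred to a t distribution with K − 2 degrees of freedom brought the type I error back to about 5–7%. Report the number of providers and the spread of patients per provider with the results.

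The cost is one sentence and one data field, and no more patients. Intervals for provider-level predictors will be somewhat wider, because the information on them is limited by the number of providers. Patient-level results should change little. The identifier is best collected from now on, since it may be hard to reconstruct later.

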### Sample size justification

Based on preliminary data from published studies, we defined a clinically significant impact to be attained at 15% reduction in the rate of CT head imaging in the published group, assuming 70% baseline CT utilization (23). Adjusting for an alpha of 5%, a total of 300 evaluable patients will be required (150/arm) to achieve at least 80% power to reject the null hypothesis. To account for patient withdrawal (change in exam before blood draw, leaving against medical advice, etc.), we will plan to target a maximum of 350 subjects enrolled.

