### Primary efficacy analysis

The primary endpoint is the proportion of patients undergoing a head CT scan which will be reported as percentage of total patients. The key hypothesis:

H_0_ (null): There is no difference in CT head scan rates between the published biomarker and blinded biomarker arms.H_1_ (alternative): The published biomarker arm has a significantly lower CT scan rate compared to the blinded biomarker arm.

To evaluate the hypothesis, we will perform univariate analysis using a Pearson’s chi-square test followed by a pre-specified logistic regression model that adjusts for stratification/randomization variables (e.g., site, age, GCS score category), providing an adjusted odds ratio (aOR) and 95% confidence interval (CI). A statistically significant result will be defined with a two-tailed *p*-value of less than 0.05, or adjusted odds ratios for predicting CT head acquisition with a 95% confidence interval below 1.0. In the event the *p*-value approaches the significance threshold (e.g., p between 0.05 and 0.10), results will be interpreted with caution, and effect size estimates will be emphasized to assess the practical impact of the observed differences.

For subgroup analysis across randomization strata, we will use the same testing as primary hypothesis. Then, we will formally test for heterogeneity of treatment effect using interaction terms in the logistic regression models. A *p* < 0.05 for the interaction will be considered evidence of differential efficacy across subgroups (given the exploratory nature of interaction testing).

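### The 300 evaluable patients (150 per arm) give about 77% power for 70% versus 55% under the stated two-tailed test, not at least 80%, and the 15% reduction is not labelled absolute or relative

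*Protocol article*

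**What the plan says.** The Sample size justification section of the protocol article takes as its target "a clinically significant impact to be attained at 15% reduction in the rate of CT head imaging in the published group". The control-arm rate behind this target comes from "assuming 70% baseline CT utilization". At an alpha of 5% the section concludes that "a total of 300 evaluable patients will be required (150/arm) to achieve at least 80% power to reject the null hypothesis". It then raises enrolment to a maximum of 350 to cover withdrawals, such as patients whose examination changes before the blood draw or who leave against medical advice.

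The Primary efficacy analysis section names the test and the criterion: "we will perform univariate analysis using a Pearson’s chi-square test", followed by a logistic regression adjusted for the stratification variables, and "A statistically significant result will be defined with a two-tailed *p*-value of less than 0.05". Allocation is 1:1 (Study design and methods). The Study objective section announces frequent interim analyses with efficacy and futility boundaries. The sample size section does not mention them.

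**The concern.** Every input to the power calculation is printed in the article: baseline rate, reduction, alpha, sidedness, test, allocation and number per arm. The claim can therefore be checked without the full protocol or analysis plan, and the stated power does not follow from those inputs. This is the only power statement for the primary endpoint, so a null result would be read against it. A reader told that power was at least 80% would put the type II error at 20% or less, whereas the stated chi-square test has about 23%.

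The phrase "15% reduction in the rate of CT head imaging in the published group" also leaves open whether the reduction is 15 percentage points or 15% of the 70% baseline. The two readings are far apart, and nothing in the text settles which effect the trial was sized to detect.

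**Working it through.** **Inputs.** Control rate p1 = 0.70, reduction 15%, alpha 0.05 and 150 per arm (Sample size justification); two-tailed Pearson chi-square (Primary efficacy analysis); 1:1 allocation (Study design and methods).

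**Formulas.** With d = p1 − p2, p̄ = (p1 + p2)/2 and n per arm (pooled variance under the null):

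- Power = Φ{ [d√n − z(α)·√(2p̄(1−p̄))] / √(p1(1−p1) + p2(1−p2)) }
- n = [z(α)·√(2p̄(1−p̄)) + z(β)·√(p1(1−p1) + p2(1−p2))]² / d²

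**1. Attempt to reproduce the plan's figure, absolute reading (70% vs 55%), two-sided 5%.**

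- p̄ = 0.625, so √(2 × 0.625 × 0.375) = √0.46875 = 0.6847
- √(0.70 × 0.30 + 0.55 × 0.45) = √0.4575 = 0.6764
- Power at n = 150: Φ[(0.15 × 12.247 − 1.960 × 0.6847)/0.6764] = Φ[(1.8371 − 1.3419)/0.6764] = Φ(0.732) = **76.8%**
- n for 80%: (1.3419 + 0.8416 × 0.6764)²/0.0225 = (1.9112)²/0.0225 = 162.3, so **163 per arm, 326 in total**

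The stated figure is not reproduced. Other two-sided methods at 150 per arm give:

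| Method | Power |
|---|---|
| Exact enumeration of the Pearson test | 76.8% |
| Unpooled variance | 77.5% |
| Arcsine | 76.9% |
| Log odds ratio | 76.1% |
| Exact, Yates correction | 73.0% |

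Without a continuity correction, these approximations need 160 to 166 per arm for 80% power. At 150 per arm, the drop detectable with 80% power is about 15.6 points.

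**2. One-sided test as an explanation.** With z = 1.645, power at 150 per arm is Φ[(1.8371 − 1.1262)/0.6764] = Φ(1.051) = 85.3%. But the number required would then be (1.1262 + 0.5693)²/0.0225 = 127.8, so 128 per arm. A one-sided design clears 80% at 150 but does not yield 150 as the requirement, and it conflicts with the two-tailed criterion.

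**3. Relative reading (70% vs 59.5%), two-sided 5%.** d = 0.105 and p̄ = 0.6475; the two square roots are 0.6756 and 0.6715.

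- Power at 150 per arm: Φ[(0.105 × 12.247 − 1.960 × 0.6756)/0.6715] = Φ(−0.057) = **47.7%** (exact Pearson 47.5%)
- n for 80%: (1.3242 + 0.5652)²/0.011025 = 323.8, so 324 per arm, 648 in total
- Power at 175 per arm: 53.8%

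**4. What the cap of 350 provides, absolute reading.** At 175 per arm, power is Φ[(0.15 × 13.229 − 1.3419)/0.6764] = Φ(0.950) = **82.9%**. The plan's allowance is 50/350 = 14.3% loss. Keeping 326 evaluable allows only 24/350 = 6.9%.

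**The case against.** **The shortfall is small.** This stands on the absolute reading: about 3 points of power, or 26 patients (8.7% of 300), with a detectable difference of about 15.6 points instead of 15. No error rate under the null and no patient protection is affected. The number is still wrong as printed, and it is cheap to correct.

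**The adjusted model may have more power.** The success rule also admits an adjusted odds ratio whose 95% interval lies below 1, and the adjustment variables are ones likely to drive CT decisions. Simulation at 150 per arm with one balanced three-level covariate gives adjusted power of about 79%, 82% and 88% for covariate odds ratios of 1.6, 2.7 and 4.5 per level. So 77% is the power of the unadjusted chi-square test, and a reader should not infer that every planned analysis falls below 80%. These covariate strengths are assumptions, however. The article gives none, and its sample size section does not rest its claim on adjustment.

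**The relative reading.** A reader might infer that the trial really has only about 48% power. The documents do not support that. The word relative never appears there, and 150 per arm lies close to the absolute requirement (163) and far from the relative one (324). The defect is the ambiguous wording.

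**Interim looks.** It is also tempting to put a figure on the power lost to interim efficacy boundaries by assuming, say, five looks. The article gives neither the number of looks nor the boundaries, and these may stand in documents not shown. All that can be said is that the figures here are for a fixed sample, and that efficacy looks which preserve the overall 5% would lower them.

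**The cap of 350 as a cure.** It cannot be taken for granted that CT status will be known for everyone randomised, because the plan itself expects withdrawals and departures against medical advice. If only 300 are analysable, as the plan allows, power stays near 77%.

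**Conclusion.** The concern holds. For an absolute drop from 70% to 55%, a two-tailed 5% Pearson chi-square test, 1:1 allocation and no interim adjustment, 150 per arm gives about 77% power, and 80% needs 163 per arm (326 evaluable). The conclusion does not depend on the choice of two-sided approximation, and a one-sided reading neither fits the stated criterion nor explains the 150.

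The missing word absolute is the second part of the point. The absolute reading is the likely one, and the 48% figure matters only as the consequence if the sponsor meant the other.

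**What to change.** 1. State the target as an absolute reduction from 70% to 55%, if that is what was meant.
2. Replace the power sentence with: *150 per arm gives about 77% power; 326 evaluable patients are needed for 80%; if all 350 are analysed, power is about 83%, before any interim adjustment.*
3. Define the primary analysis set as all randomised patients with a known CT status, in line with the intention-to-treat analysis mentioned under Rationale for randomization. State that 80% power tolerates about 7% loss from 350, not 14%.
4. Recompute power with the actual interim boundaries and report that figure.

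The cost is wording, one recalculation and a slightly less favourable stated power at 300 patients. On the absolute reading the maximum of 350 is unchanged. If the sponsor meant a relative reduction, rewording is not enough: 648 evaluable patients would be needed, and either the target effect or the sample size would have to be reconsidered.

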### Pre-randomization procedures

Screening of eligible patients will be performed by study personnel via real-time tracking of ED dashboard for new admissions or transfers. Triage notes and evaluations will be reviewed for primary eligibility based on age, type of injury, reported GCS, timing of injury and whether existing head imaging is present. If subjects pass screening, they will be approached for review of detailed inclusion and exclusion criteria and for consent process. Written informed consent (from the patient or legally authorized representative) is obtained before any study-specific activities. Providers are notified about patient enrollment and requested to hold off on obtaining CT head imaging until randomization and biomarker data is available. Randomization variables will then be obtained, and subjects will be randomized using an automated algorithm implemented in RedCap into published or blinded biomarker groups.

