### Procedures for blinded biomarker arm

For the blinded arm, no further changes are requested from the provider, and a venous blood sample is then collected for point-of-care GFAP and UCH-L1 measurement using the i-STAT TBI cartridge; results are withheld from clinicians. The patient will then be followed up during the hospitalization for reviewing provider decisions, imaging data, clinical outcomes, and disposition as listed in the outcome section.

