### Rationale for randomization

Randomization ensures that known and unknown confounders–such as injury mechanism, clinician decision-making patterns, and patient comorbidities–are evenly distributed between the biomarker-published and biomarker-blinded arms, thereby allowing unbiased estimation of the causal effect of real-time biomarker disclosure on head-CT utilization. Stratification by age, biological sex, race, GCS score and Canadian CT Head Rule risk category further improves balance across prognostic variables. Randomization is essential in this trial because CT decisions are inherently subjective, and without allocation concealment, selection bias or preferential imaging decisions could distort observed differences. The 1:1 parallel-group design also facilitates straightforward intention-to-treat analysis and preserves statistical validity in interim monitoring.

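### Randomising before the blood draw puts pre-draw losses inside the randomised set, where dropping them can bias the CT comparison and keeping them dilutes it

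*Protocol article*

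**What the plan says.** All places are in the protocol article, under Methods and analysis.

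- **Order of events.** Pre-randomization procedures ends with allocation: "subjects will be randomized using an automated algorithm implemented in RedCap". No blood draw is described before that step. Procedures for blinded biomarker arm then says "a venous blood sample is then collected for point-of-care GFAP and UCH-L1 measurement". Table 3 agrees: biomarker testing is marked at allocation and post-allocation, not at enrolment. Study design and methods calls the trial open-label.
- **Sample size.** Sample size justification assumes a "15% reduction in the rate of CT head imaging in the published group, assuming 70% baseline CT utilization" and concludes: "Adjusting for an alpha of 5%, a total of 300 evaluable patients will be required (150/arm) to achieve at least 80% power". The margin is explained by "To account for patient withdrawal (change in exam before blood draw, leaving against medical advice, etc", and the total is given as "we will plan to target a maximum of 350 subjects enrolled". Study objective and Study design and methods both give 350 as the number randomised 1:1.
- **Endpoint.** Primary efficacy analysis uses head CT, yes or no, reported as a percentage of total patients. Post-randomization in-hospital assessment captures CT from allocation onward. Neither needs a biomarker result.
- **Analysis principle.** Rationale for randomization says that the 1:1 design "facilitates straightforward intention-to-treat analysis". This is a remark on the design and does not define the primary analysis set.

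**The concern.** Both named reasons for loss are tied to the primary endpoint. A change in the exam is a plausible reason to scan, and leaving against advice plausibly means no scan. Neither makes head CT unobservable by nature, so calling these patients non-evaluable is a choice, not a necessity of missing data.

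Because allocation comes first, these patients already belong to an arm when they are lost, and the treating provider may know which arm. Removing them would condition the comparison on something related to the outcome and possibly to the arm. Retaining them is the sound analysis, but an unsampled patient in the published arm has no result to release, so that patient cannot contribute the assumed effect. The order of steps therefore forces a choice between a risk of bias and a loss of power, and the power statement allows for neither. Counting power on an evaluable subset also sits badly with a percentage of total patients and with the intention-to-treat remark.

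**Working it through.** **Inputs.** CT rate 70% in the blinded arm and 55% in the published arm (the 15% read as percentage points); two-sided 5% ("A statistically significant result will be defined with a two-tailed" p-value below 0.05); 300 evaluable; 350 randomised, 175 per arm. All are from Sample size justification, Primary efficacy analysis and Study design and methods. Loss splits by arm and CT rates among the lost are not in the documents and are assumed below. Interim looks are ignored throughout.

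**1. The plan's own figures.** The inflation reproduces: 300/(1 − 50/350) = 350, a 14.3% allowance. The base does not. With the pooled normal approximation,

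n per arm = [1.960·√(2·0.625·0.375) + 0.842·√(0.70·0.30 + 0.55·0.45)]² / 0.15² = 162.3, so 163 per arm, 326 in total.

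Power at 150 per arm is 76.8%. This shortfall is a separate matter, and the present point does not depend on it.

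**2. If the 50 are dropped.** Suppose there is no true effect, with 70% scanned in both arms (122.5 of 175):

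| Lost, published / blinded | CT rate among lost, published / blinded | Published | Blinded | Apparent reduction | Chance of p < 0.05 |
|---|---|---|---|---|---|
| 25 / 25 | 70% / 70% | 70.0% | 70.0% | 0 | 5% |
| 25 / 25 | 100% / 100% | 65.0% | 65.0% | 0 | 5% |
| 35 / 15 | 100% / 100% | 87.5/140 = 62.5% | 107.5/160 = 67.2% | 4.7 points | 14% |
| 40 / 10 | 100% / 100% | 82.5/135 = 61.1% | 112.5/165 = 68.2% | 7.1 points | 25% |
| 15 / 35 | 100% / 100% | 67.2% | 62.5% | −4.7 points | 14% |
| 25 / 25 | 90% / 50% | 66.7% | 73.3% | 6.7 points | 24% |

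Equal losses with equal CT rates do no harm. Unequal ones can push the estimate either way.

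The sign also depends on which reason for loss dominates. Take a true 15-point effect (96.25 of 175 scanned in the published arm) and lose 12 published and 4 blinded patients:
- all of them scanned: (96.25 − 12)/163 = 51.7% against (122.5 − 4)/171 = 69.3%, a difference of 17.6 points;
- none of them scanned: 96.25/163 = 59.0% against 122.5/171 = 71.6%, a difference of 12.6 points.

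**3. If the 50 are kept.** Assume 25 per arm are never sampled and have the same CT rate q in both arms. The difference shrinks to 15 × 150/175 = 12.9 points.
- q = 70%: published (82.5 + 17.5)/175 = 57.1%, blinded (105 + 17.5)/175 = 70.0%. Power is 70.7%; 80% would need 438 randomised.
- q = 100%: published (82.5 + 25)/175 = 61.4%, blinded (105 + 25)/175 = 74.3%. Power is 73.3%; 80% would need 412 randomised.

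**The case against.** The strongest reply is that no exclusion is ever stated. Evaluable appears in the sample-size paragraph as a power input, while the analysis text speaks of total patients and the rationale invokes intention-to-treat. Defining the analysis population is properly left to a SAP that is not shown. This stands as far as it goes: the article does not say that these patients will be removed. It does not dispose of the point, because the article itself fixes the moment of randomisation. A SAP can define the analysis set but cannot move allocation, and keeping everyone brings the dilution in step 3.

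A second reply is that enrolled may mean consented, since Table 3 separates enrolment from allocation, so some losses could precede randomisation. That is possible for some of them, but two sections give 350 as the number randomised.

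Four stronger readings are tempting, and the documents do not support them:
- *The bias favours the published arm.* No losses by arm are given, and the 12/4 example reverses when the lost patients are unscanned.
- *Only the published arm waits.* Pre-randomization procedures asks providers of all enrolled patients to hold CT until randomisation and biomarker data are available, whereas the blinded-arm section asks nothing further of the provider. These passages need to be reconciled. In any case, the wait for a result follows the draw.
- *CT status is on record for everyone lost.* The losses are called withdrawals. Use of the record may end with consent, and a patient who leaves may be scanned elsewhere.
- *Keeping all 350 gives about 83% power.* The figure of 82.9% requires the full effect in patients who never had a sample.

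**Conclusion.** The point holds in a conditional form. Randomisation before the draw, together with a power basis of 300 evaluable out of 350 randomised, leaves up to 14.3% of randomised patients lost for reasons related to the endpoint. Dropping them can bias the primary comparison if losses or their CT rates differ by arm. In the illustrations with no true effect, that produces apparent differences of up to about 7 points in size, but the splits are assumed, and neither direction nor size can be learned from the documents. Keeping them gives power of about 71% to 73% against the planned 80%. That range assumes 25 unsampled patients per arm, no effect in them, CT rates of 70% to 100% among them, a 15-point effect in everyone else and no interim looks. A reader should not conclude that a biased analysis is planned, only that the design creates the problem and the text does not resolve it. It should be changed before the trial depends on it.

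**What to change.** 1. Perform the REDCap randomisation immediately after the venous sample is drawn. Both arms are sampled in any case, so a change in exam or a departure before the draw then falls before allocation. It leaves the randomised set without any outcome-related exclusion and without diluting the effect.
2. State that the primary analysis includes all randomised patients as allocated, whatever happens with the cartridge and whether or not they leave early. Add a sensitivity analysis for patients whose CT status is unknown because consent was withdrawn or the scan was done elsewhere.
3. Restate power on that randomised set, with an explicit assumption about patients who are randomised but never have a usable result, and do not use evaluable as if it defined the analysis population.
4. Reconcile the passages on holding CT in the pre-randomisation and arm-specific sections, so that the handling of each arm before and after allocation is unambiguous.

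The cost is a change in the order of steps in the protocol and in REDCap, plus a few sentences on the analysis set and sample size. Some patients will be sampled but never randomised, in a number the documents do not let one estimate. Losses after the draw, such as failed cartridges and later departures, remain and are handled by items 2 and 3.
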